### Outcomes

2.3

#### Primary outcomes

2.3.1

Primary outcomes include progression-free survival (PFS): the time from treatment to disease recurrence or death due to disease progression; and OS: the time from the beginning of treatment to death due to any cause. These 2 indicators are calculated at the end of the trial.

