**Methods::**

This study is a multicenter observational cohort trial taking 2 years. A total of 620 patients will be allocated at a ratio of 1:1 to receive TCM or not. The primary outcomes are progression-free survival (PFS) and overall survival (OS), which are calculated at the end of the trial. Secondary outcomes include TCM symptoms, Karnofsky Performance Status (KPS), ECOG score, European Organization for Research and Treatment of Cancer (EORTC) Breast-Cancer-Specific Quality of Life Questionnaire (EORTC QLQ-BR23), as well as clinical indicators including tumor markers, immune function evaluation, chest computed tomography/magnetic resonance imaging, and abdominal B-ultrasound. Assessments will be performed at baseline and 3, 6, 9, 12, 16, and 20 weeks after observation.

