The purpose of this study is to evaluate whether the intervention of TCM can improve the postoperative TNBC patients with disease-free survival (DFS) and overall survival (OS), and then provide strong evidence that TCM treatment has exact effects and obvious advantages. Meanwhile, this study can establish TNBC patient information database, which may contribute to the correct guideline for TNBC patients with TCM treatment, build harmonious relationship between doctors and patients, increase TNBC patients’ compliance, and enhance the confidence to overcome the disease.

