### Sample size

2.2

Considering the results of the study at MD Anderson Cancer Center in foreign countries^[15]^ showed that the 3-year survival rate of TNBC patients was significantly shorter than that of non-TNBC patients (74% vs 89%, *P* < .01), as well as the lost rate of 20%, the sample size (N) is calculated by the following formula: 
[figure not shown]

*P*_0_ means the recurrence and metastasis rate of the nonexposed group; *P*_1_ represents the recurrence and metastasis rate of the TCM exposure group, *P*_1_ = RR × *P*_0_, where RR is the relative risk caused by exposure factors.

This study assumes that α = 0.05 and β = 0.10. According to the related study, the rate of recurrence and metastasis was 12% in the TCM group and 33.33% in the western medicine treatment group, respectively. The relative risk (RR) of TCM intervention was that RR = 12%/33.33% = 0.36. Domestic and foreign data showed that the 2-year recurrence and metastasis rate of TNBC patients was 17%, so *P*_0_ = .17, *P*_1_ = RR × *P*_0_ = 0.06.

Substituting the formula, the calculated amount of each group is as follows: 

Considering the 20% of drop rate, the confinement factor in different hospitals increased by 10% of the sample size, that is, at least 249 (N ≥ 249) cases should be observed in each group. Then, combined with the study period and the target population distribution of the study unit, 310 cases should be included in the Chinese medicine and Western medicine groups, respectively, in this study.

Before the research, investigators are responsible for the introduction the clinical research related matters and the records of the baseline data, then all participants sign the informed consent form. Patients in the TCM exposure group take Chinese medicine (San Yin Decoction) as well as original Western medicine, while patients in the nonexposed group only receive Western medicine treatment. The study will be performed during 2 years, and all results are recorded according to the Case Report Form (CRF).

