### Inclusion and exclusion criteria

2.5

Participants’ inclusion criteria are as follows: The primary BC after surgical treatment, the pathological diagnosis of breast epithelial tumors (BC), ER, PR, and Her-2 immunohistochemical results were negative; no recurrence of metastasis; KPS score ≥ 60 points; aged 18 to 75 years (including 18 and 75 years); no serious organic or functional disorders, no drugs, and food allergy; and willing to receive treatment, observation, and inspection.

Participants’ exclusion criteria are as follow: do not meet the inclusion criteria; patients expected to survive < 6 months; complicated with cardiovascular and cerebrovascular, liver, kidney, hematopoietic system of serious primary disease, and mental illness; breastfeeding, pregnancy, or women preparing for pregnancy; allergies and allergies to a variety of drugs; and participating in other drug subjects.

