### Statistical analysis

2.6

SPSS 18.0 (SPSS, lnc., Chicago, IL), Stata10.0 (StataCorp, College Station, Texas), and other statistical software are used for data analysis with a 2-sided significance level of 0.05, the point estimate, and 95% confidence interval. If the data obey the normal distribution and the variance is homogeneous, data are expressed as the number of cases (n) and the mean ± standard deviation (SD). Before and after treatment at multiple time points, measurement data using repeated measurement of variance analysis and multiple variance analysis are expressed as median (M), minimum (min), and maximum (max). The Kruskal–Wallis H test is used to compare the data between the 2 groups. The numerical variables are measured at multiple time points before and after treatment, and the generalized estimating equations or mixed effect models are used for the classification and sorting variables. If the analysis index is disordered using χ^2^ test, the analysis index is ordered with rank sum test, the 2-way ordered attribute of different data using linear χ^2^ test, and rank sum test. The survival rate is calculated by Kaplan–Meier method (K-M method), and the survival curve is drawn. Multivariate data are analyzed using multiple linear regression analysis, COX regression analysis, trend testing, and so on.

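### The primary PFS counts only recurrence and progression-related death, which does not match the stated disease-free survival aim in resected, recurrence-free patients

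*Protocol article*

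**What the plan says.** All references are to the protocol article.

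- **Primary outcomes (2.3.1).** PFS is "the time from treatment to disease recurrence or death due to disease progression". The same sentence gives "OS: the time from the beginning of treatment to death due to any cause". The abstract repeats the pairing: "The primary outcomes are progression-free survival (PFS) and overall survival (OS), which are calculated at the end of the trial". The abstract's Discussion paragraph also names PFS and OS.
- **Background, purpose of the study.** The question is whether TCM can "improve the postoperative TNBC patients with disease-free survival (DFS) and overall survival (OS". DFS appears nowhere else and is not defined.
- **Inclusion criteria (2.5).** "The primary BC after surgical treatment", with "no recurrence of metastasis".
- **Sample size (2.2).** The planning quantity is neither PFS nor DFS: P0 "means the recurrence and metastasis rate of the nonexposed group", and P1 is the same rate in the TCM group.
- **Statistical analysis (2.6).** "The survival rate is calculated by Kaplan–Meier method (K-M method), and the survival curve is drawn". Cox regression is also listed. No competing-risks method is named.

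**The concern.** The purpose, the primary outcome and the sample size name three different endpoints: DFS, a cause-restricted PFS, and the rate of recurrence and metastasis. The restriction on death in PFS is not loose shorthand, because the same sentence uses all-cause death for OS.

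Three things follow if the definition is applied literally.

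1. A patient who dies without recurrence, from toxicity, comorbidity or an unknown cause, has no PFS event. Kaplan–Meier and Cox handle a non-event by censoring. A Kaplan–Meier curve built that way overstates the probability of recurrence and does not estimate disease-free survival.
2. Each death without documented recurrence needs a judgement on cause before it can be classified. Groups are formed by whether patients take TCM, and no blinding is described, so attribution could move a primary endpoint. Counting all deaths removes that judgement.
3. The TCM group receives a decoction in addition to Western treatment. A death caused by the added treatment would not count against it in this endpoint.

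**Working it through.** **Inputs from the article.** P0 = 0.17 (2-year recurrence and metastasis rate); RR = 12%/33.33% = 0.36; α = 0.05 two-sided; β = 0.10; 20% loss; a 10% centre factor; at least 249 per group; 310 per group planned. **Assumed:** q, the 2-year probability of death without recurrence that is not attributed to progression. The article gives no figure for it.

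**Step 1: reproduce the plan's figure.** P1 = 0.36 × 0.17 = 0.0612. The usual two-proportion formula is n = [z(0.975)·√(2p̄(1−p̄)) + z(0.90)·√(P0(1−P0) + P1(1−P1))]² / (P0−P1)², with p̄ = (0.17 + 0.0612)/2 = 0.1156. It gives 180 per group. Then 180/0.8 × 1.1 = 248, or 180/0.8/0.9 = 250. Both agree with the stated 249. The article's own formula is not visible, so the exact route is unknown. The sample-size arithmetic is not at fault here.

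**Step 2: expected events under the plan.** Controls: 310 × 0.17 = 52.7. TCM: 310 × 0.0612 = 19.0. Ratio 0.36.

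**Step 3: count all deaths.** Assume 0.5–1% per year, so q = 1–2% over 2 years, equal in both groups, and add these deaths to the events above.

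| q over 2 years | Added per group | TCM | Control | RR |
|---|---|---|---|---|
| 1% | 3.1 | 22.1 | 55.8 | 0.40 |
| 2% | 6.2 | 25.2 | 58.9 | 0.43 |

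The added deaths equal 16–33% of the expected TCM-group events (3.1/19.0 and 6.2/19.0) and 6–12% of the control-group events (3.1/52.7 and 6.2/52.7). Using 248 evaluable patients instead of 310 scales every count by 0.8 and leaves the ratios unchanged.

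**Step 4: allow for overlap, and check power.** Simple addition assumes that none of these deaths follows a recurrence already counted. Treating the two event types as independent gives a two-year event probability of 1 − (1 − P)(1 − q). The article's rounded P1 = 0.06 is used here, and 310 × 0.8 = 248 evaluable per group.

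| q | Control | TCM | RR | n per group for 90% power, before inflation | Power at 248 |
|---|---|---|---|---|---|
| 0 | 17.0% | 6.0% | 0.35 | 175 | 97.2% |
| 1% | 17.8% | 6.9% | 0.39 | 191 | 96.0% |
| 2% | 18.7% | 7.9% | 0.42 | 207 | 94.5% |
| 3% | 19.5% | 8.8% | 0.45 | 223 | 92.9% |
| 5% | 21.2% | 10.7% | 0.51 | 256 | 89.1% |

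The two approaches agree closely. The expected effect weakens as q rises, but power falls just below 90% only at q = 5%. These are unadjusted two-proportion figures at the plan's own effect size. They compare endpoint definitions only.

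**The case against.** The strongest reply is that this is mostly a labelling problem. Recurrence is the first event in the definition and suits a resected cohort. DFS appears once, undefined, while the abstract's purpose speaks of recurrence and metastasis rate and survival rate. A recurrence-centred endpoint beside all-cause OS would match that purpose and the sample-size basis. Part of this stands: the endpoint can be measured, and the absence of measurable disease at entry makes PFS a poor name without making the outcome undefined. But the Background sets DFS as the aim, and the definition as written leaves out some deaths that the usual DFS counts.

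Other parts of the reply succeed against stronger readings that a reader might infer:

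- **That treatment-related deaths are hidden from the trial.** They are not. OS is also primary and counts every death, section 2.7 requires serious adverse events to be reported within 24 hours, and 2.3.2 includes safety monitoring.
- **That the plan says other deaths are censored.** It does not. This is implied by the event definition and the named methods. The list of methods in 2.6 is open-ended, and a fuller plan may say more.
- **That unblinded investigators will assign cause of death.** The article does not say who does so, and an article may leave out adjudication. Section 2.4 describes tests to confirm recurrence, so attribution matters only for deaths without documented recurrence.
- **That the size of the study is undermined.** The assumed death rate has no source in the article, and exclusion of serious organ disease points to its lower end. Power holds across 1–2%.

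**Conclusion.** The point stands as a conflict between a primary outcome and the objective it should answer. Taken literally, PFS leaves out deaths without recurrence that are not put down to progression, so it is not disease-free survival, and it depends on cause attribution where no blinding is described. The gap is confined to this endpoint, since OS and safety reporting capture those deaths.

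On the assumption of 1–2% such deaths over 2 years, equal in both groups, the planned RR of 0.36 becomes about 0.40–0.43, with power of about 94–96% at 248 evaluable per group. If the rates differed between groups, the shift could be larger or go the other way, and nothing in the article allows that to be sized. The conflict of definitions does not depend on these figures. The defect lies in what the endpoint measures; the number of patients is adequate for the corrected one.

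**What to change.** - **Abstract (Methods and Discussion) and 2.3.1:** replace PFS with DFS, defined as the time from one stated origin to the first of local or regional recurrence, distant metastasis, or death from any cause. The origin must be named, and must be the same for both groups and for OS. At present one outcome runs from treatment and the other from the beginning of treatment, without saying which treatment is meant.
- **Sensitivity analysis:** keep the cause-restricted endpoint, with other deaths treated as competing events.
- **2.2 Sample size:** state that P0 and RR are recurrence and metastasis rates, so the expected effect on DFS is slightly less favourable than 0.36. The planned 310 per group can stay under the assumptions above.

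**Cost.** All-cause death is already needed for OS, so no new data are required. The expected effect is slightly smaller. The change alters a primary endpoint of a registered study that began recruiting in January 2017, so it needs a dated, documented amendment with its reason, ideally made before outcome data are compared by group.

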### Design

2.1

The study is a multicenter observational cohort trial lasting 2 years in 5 locations, including Longhua Hospital affiliated to Shanghai University of TCM, Shuguang Hospital affiliated to Shanghai University of TCM, Yueyang Hospital of integrated Chinese and Western Medicine, Zhejiang Provincial Hospital of TCM, and Fudan University Shanghai Cancer Center. All the eligible TNBC patients are divided into 2 cohorts: TCM exposure group and nonexposed group, according to whether taking TCM treatment (Fig. 1). Participants in the nonexposed group receive preoperative chemotherapy and/or radiotherapy, as well as postoperative biological agents after surgery, according to the National Comprehensive Cancer Network (NCCN) Breast Cancer Treatment Guidelines. Participants in the TCM exposure group receive TCM combined with Western medicine treatment. TCM treatment is based on syndrome differentiation by inspection, listening and smelling, interrogation, pulse-taking, and palpation, and then provide the most appropriate decoction.

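### PFS and OS start at an undefined treatment date that can differ between cohorts and precede a recurrence-free enrolment, so the primary comparison can be biased in either direction

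*Protocol article*

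**What the plan says.** Section 2.3.1 (Primary outcomes) defines PFS as "the time from treatment to disease recurrence or death due to disease progression" and OS as "the time from the beginning of treatment to death due to any cause". Neither definition names the treatment or links it to surgery, consent or the baseline visit.

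Other sections determine what the word can mean:

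- **Nonexposed cohort (2.1 Design):** "Participants in the nonexposed group receive preoperative chemotherapy and/or radiotherapy, as well as postoperative biological agents after surgery". Its only treatment is Western and can begin before the operation.
- **Exposed cohort (2.1 Design):** "Participants in the TCM exposure group receive TCM combined with Western medicine treatment". Section 2.2 adds: "Patients in the TCM exposure group take Chinese medicine (San Yin Decoction) as well as original Western medicine". The word for the Western component suggests that it may already be under way when TCM begins. These patients have two candidate start dates.
- **Exposure (2.1 Design):** cohorts are formed "according to whether taking TCM treatment", with no date by which this is settled.
- **Eligibility (2.5):** "The primary BC after surgical treatment", together with "no recurrence of metastasis; KPS score ≥ 60 points". Entry is postoperative and requires freedom from recurrence.
- **Analysis (2.6):** Kaplan–Meier curves and Cox regression.

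**The concern.** This is a non-randomised comparison, so no randomisation date aligns the two clocks. The stated time origin has to do that, and as worded it does not.

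Two natural readings cause trouble.

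1. **Treatment means each cohort's own treatment.** The exposed clock starts with TCM. The nonexposed clock starts with Western therapy, possibly before surgery. Nonexposed patients then carry event-free time before enrolment that exposed patients lack, and the bias runs against TCM.
2. **Treatment means first anticancer treatment.** Both cohorts carry event-free time before enrolment. A patient who begins TCM late must also stay recurrence-free until then to be counted as exposed, so the exposed cohort may carry more of it. The bias then favours TCM.

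In either case patients are counted as at risk over a period in which, given the entry rule, they could not have had the event. Both primary outcomes share this origin.

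**Working it through.** **Inputs from the protocol article, section 2.2:** two-year recurrence and metastasis rate P0 = 0.17; RR = 0.36, so P1 = 0.36 × 0.17 = 0.0612 (printed as 0.06); α = 0.05 (two-sided in section 2.6); power 0.90; minimum 249 and planned 310 per group.

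**Plan's own figure.** The two-proportion formula with pooled variance under the null gives 179.4 per group for P1 = 0.0612, and 179.4 / (0.8 × 0.9) = 249.2. With P1 = 0.06 it gives 174.7, and 174.7 / 0.7 = 249.5. The stated 249 is reproduced. The time origin does not enter this calculation.

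**Assumptions that are not in the article:** no true effect, constant hazard, no dropout, 24 months of follow-up after an event-free enrolment, and the lead times themselves (time from the clock's start to enrolment).

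**Step 1, hazard.** −ln(1 − 0.17) / 24 = 0.00776 per month.

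**Step 2, effect on one cohort's rate.** With a fixed lead time L, the apparent 24-month event rate is 1 − exp(−0.00776 × (24 − L)):

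- L = 0: 17.0%
- L = 6: 13.0%
- L = 12: 8.9%

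**Step 3, hand check of the comparison.** Mean time at risk after enrolment is 0.17 / 0.00776 = 21.9 months. Adding 6 months to one cohort only gives a ratio of crude event rates of 21.9 / 27.9 = 0.785, or 27.9 / 21.9 = 1.27 if the other cohort has the extra time. Cox regression moves further from 1, because early events in one cohort are set against patients in the other who cannot yet have an event.

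**Step 4, Cox simulation.** 310 per group, lead times uniform around the stated mean, 300 runs per row. The Monte Carlo standard error is about 1.3 percentage points at a 5% rate and 2.7 at 32%.

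| Mean lead time, exposed / nonexposed (months) | HR, no delayed entry | False positives | HR, delayed entry | False positives |
|---|---|---|---|---|
| 6 / 0 | 0.73 | 33% | 0.99 | 6% |
| 12 / 0 | 0.48 | 88% | 0.99 | 3% |
| 12 / 6 | 0.73 | 32% | 0.99 | 5% |
| 0 / 6 | 1.33 | 31% | 1.01 | 3% |
| 6 / 6 | 0.99 | 5% | 1.00 | 4% |

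A separate simulation with fixed lead times in one cohort only, and both clocks cut at 24 months (500 runs), gave HR 0.86, 0.73 and 0.49 for 3, 6 and 12 months, with false-positive rates of 10%, 28% and 89%.

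**Reading.** The difference in lead time between cohorts drives the bias. Equal lead times lower the apparent event rates in both cohorts but leave the comparison intact. Counting risk time only from enrolment removes the problem in every row.

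**The case against.** The strongest reply is that a harmless reading exists. Section 2.2 describes baseline recording and consent before the study and then sets out what each cohort takes. Section 2.3.2 compares TCM symptom scores before and after treatment. On that reading treatment means on-study treatment from enrolment, the origin is common, and there is no guaranteed time. Figure 1 and Table 4 are not visible here and might settle the matter.

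This stands in part. The reading is possible, but section 2.3.1 does not state it. It also fits poorly with section 2.1, where nonexposed treatment includes therapy given before surgery although entry comes after surgery.

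A second reply is that exposed patients also receive Western treatment, so lead times could be similar in both cohorts. That is correct, and in that case the comparison is not biased. Nothing in the article makes them similar.

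A third reply is that delayed entry and time-dependent exposure are usually left to an analysis plan, and that an article need not state a maximum time since surgery. That is accepted, and neither absence is part of this point. The point is the wording of an endpoint definition that the article does give.

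A reader might infer that the starting dates do differ, that many patients were treated before enrolment, or that the result will favour TCM. The article supports none of these. It reports no dates or intervals, and the direction of any bias is unknown.

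**Conclusion.** The point holds as a defect in the stated definition. The origin of both primary outcomes is not one identifiable date, and two natural readings count event-free time before enrolment as time at risk. The comparison **can** be biased; the article does not show that it **is**.

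For recurrence, a 6-month difference between cohorts would be enough to produce an apparent hazard ratio of about 0.73 or 1.33 with no true effect, and roughly six times the nominal 5% error rate. This rests on the plan's 17% rate, a constant hazard, full follow-up of 310 per group and assumed lead times. It does not carry over to OS, for which the article gives no two-year rate. If lead times are equal, or treatment means enrolment for everyone, there is no bias from this source.

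It should be corrected before analysis, because it affects both primary outcomes and the correction is simple.

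**What to change.** **In 2.3.1:** define time zero for PFS and OS, in both cohorts, as the date of enrolment (baseline visit). Classify TCM exposure at that date.

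**In 2.6:** adjust the Cox model for time since surgery. A common origin at enrolment does not by itself make the cohorts alike in how long after surgery they enter.

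**Sensitivity analyses:** (a) run the clock from surgery, with delayed entry at enrolment in the Cox model and the Kaplan–Meier risk sets; (b) treat TCM started after baseline as a time-dependent covariate. The baseline classification stays primary, because (b) addresses a different question.

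**Cost:** wording in two sections. The dates of surgery, enrolment and TCM start must be recorded for each patient; the case report form is not shown, so this needs checking. Reported survival times will be shorter than if counted from first treatment, and less directly comparable with series that count from there. The 249 minimum and the planned 310 per group are unaffected.
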